### Data collection

CHWs will collect baseline data, health counseling activities, and follow-up visit information using digitized forms via the REDCap® system. Data collected will include:
-Sociodemographic variables: age, sex, and health insurance affiliation.-Lifestyle behaviors: tobacco/vape use, alcohol consumption, and weekly physical activity.-Clinical measures: systolic and diastolic blood pressure.-Anthropometric measurements: weight, height, body mass index (BMI), waist circumference, hip circumference, and waist-to-hip ratio.-Cardiovascular risk scores: calculated using WHO tools.-Laboratory results will be obtained from the clinical laboratories of the assigned primary care providers, as recorded in individual service provision records.

### Blood pressure measurement

Blood pressure will be assessed using a strictly standardized protocol. Participants will be instructed to avoid caffeine, smoking, and physical activity for at least 30 min before the assessment. The appropriate cuff size will be selected according to mid-arm circumference, and blood pressure readings will be recorded using a calibrated device in accordance with the manufacturer's specifications. Blood pressure will be measured with the participant seated comfortably after a rest period of at least 5 min in a quiet environment. During the measurement period, participants will remain seated with their back supported, feet flat on the floor, and legs uncrossed. The arm used for measurement will be uncovered and supported at heart level. Three consecutive measurements will be obtained at 1- to 2-minute intervals using validated automated upper-arm devices. For analysis, the average of the last two readings will be used to improve accuracy and reduce short-term variability. To minimize misclassification related to the white-coat effect, out-of-office blood pressure monitoring will be recommended when clinically indicated. All procedures will be conducted in accordance with the recommendations of the International Society of Hypertension (ISH) guidelines, ensuring methodological rigor and reproducibility (2).

### Sample size

Based on the findings of a meta-analysis by Mills et al. (8), the primary efficacy outcome sample size calculation assumed a 7-mmHg reduction in SBP (SD 50) after 12 months of follow-up, and a correlation of 0.3 between baseline and follow-up measurements. Using 90% statistical power and a two-sided significance level of 5%, the required initial sample size was estimated at 1,912 participants, increasing to a final sample size of 2,294 after allowing for approximately 20% lost, with participants recruited proportionally across provinces.

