## Methods

### Study design

RE-HOPE will be a sequential mixed methods design study comprising two phases.

In the qualitative phase, we will conduct a study within the interpretive paradigm using a phenomenological design. Focus groups with stakeholders will be conducted using a semi-structured interview guide developed by the research team. Meetings will be held at participants' workplaces, and each session will be audio-recorded, transcribed verbatim, validated, and coded. Eligible professionals will be contacted by telephone and invited to participate voluntarily. Barriers to hypertension control identified during the formative phase, including difficulties in patient identification and challenges in coordination among health system actors affecting the delivery of cardiovascular risk programs, will be incorporated into the intervention design. Accordingly, the intervention seeks to reduce gaps in screening, improve awareness of hypertension, and strengthen healthcare professionals' knowledge of the diagnosis, treatment, and control of hypertension.

The second phase will consist of a quantitative study aimed at assessing the effectiveness of the implemented strategy. A single-arm intervention design will be used to evaluate longitudinal changes in blood pressure through within-participant comparisons of baseline and follow-up measurements.

The RE-HOPE study will be conducted in primary healthcare centers in Santander, Colombia. This manuscript describes the intervention protocol and follow-up procedures implemented by the community health team.

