### Follow-up

CHWs will arrange appointments for home follow-up visits (months 1, 3, 6, 9, and 12), and blood pressure will be measured according to the standardized protocol. Additional data will be collected on anthropometric variables, physical activity habits, tobacco and alcohol use. The follow-up framework aligns with the guidelines of the International Society of Hypertension for hypertension management and the WHO guidelines (2, 15). Barriers to accessing antihypertensive medications and statins within the healthcare system will also be evaluated. If participants are found to have uncontrolled hypertension, they will be referred to their corresponding primary care center for medical evaluation and adjustment of antihypertensive therapy. In cases of critically elevated blood pressure (>180/100 mmHg), with or without signs of target organ damage, emergency care will be recommended.

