### Outcomes and measurements

The primary outcome is the change in systolic blood pressure levels from baseline to 12 months.

Secondary outcomes include:
−Systolic and diastolic blood pressure levels from baseline to 12 months.−Proportion of participants achieving systolic blood pressure control (<140 mmHg) from baseline to 12 months.−Changes in the prevalence of healthy behaviors (including reduced tobacco use and alcohol consumption, and regular physical activity).−Proportion of non-institutionalized individuals with hypertension (i.e., those not enrolled in cardiovascular risk management programs).−Change in cardiovascular risk score using the WHO risk prediction tools (16).−Identification of barriers and facilitators related to cardiovascular risk management.−Change in CHWs' cognitive and attitudinal competencies, assessed through knowledge, attitudes, and practices questionnaires administered to primary care health personnel.

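### The required sample size of 1,912 does not follow from the stated inputs for a single-arm paired design, which need about 753

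*Protocol article*

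**What the plan says.** Under Study design, the protocol article describes the quantitative phase as follows: "A single-arm intervention design will be used to evaluate longitudinal changes in blood pressure through within-participant comparisons of baseline and follow-up measurements". The limitations paragraph of the Discussion confirms that there is no comparator group. Under Outcomes and measurements, "The primary outcome is the change in systolic blood pressure levels from baseline to 12 months".

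The Sample size section, citing a meta-analysis, "assumed a 7-mmHg reduction in SBP (SD 50) after 12 months of follow-up, and a correlation of 0.3 between baseline and follow-up measurements". With 90% power and a two-sided 5% level it concludes that "the required initial sample size was estimated at 1,912 participants", and raises this to 2,294 for losses of about 20%. It names no formula, does not say whether 50 is the SD at one visit or the SD of the change, and mentions no design effect.

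**The concern.** A correlation between baseline and follow-up is what turns a per-visit SD into the SD of a within-person change, so the inputs look like those of a paired calculation. Put through that calculation, they give a number far below 1,912.

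The article prints a full set of inputs and a result, and the two do not agree. This goes beyond detail left to a fuller document. The paragraph is also the article's only justification for enrolling 2,294 people. As it stands, a reader cannot tell what effect the study is sized to detect, and the stated 90% power is not the power that the stated inputs give.

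**Working it through.** **Inputs** (Sample size section, protocol article): difference 7 mmHg; SD 50; correlation 0.3; power 90%; two-sided 5%. Design (Study design section): one arm, paired.

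**Constant.** k = (1.960 + 1.2816)² = 10.507.

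**Attempt to reproduce 1,912 with the paired formula.**
- SD of change = 50 × √(2 × (1 − 0.3)) = 59.16 mmHg.
- n = k × 59.16² / 7² = 10.507 × 3,500 / 49 = 750.5, so 751. The t-based calculation gives 753.
- 1,912 / 753 = 2.54. The stated figure is not reproduced.

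**Other single-arm readings, same power and level.**

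| Reading | n (normal) | n (t) |
|---|---|---|
| SD 50 per visit, correlation 0.3 | 751 | 753 |
| SD 50 is the SD of the change | 537 | 539 |
| SD 50 per visit, correlation ignored (0) | 1,073 | 1,075 |

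Using the 6.6 mmHg that the Introduction reports from the meta-analysis in place of 7 gives 10.507 × 3,500 / 43.56 = 844.3, so 845. None of these comes near 1,912.

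**What 1,912 would require.** The SD of change would have to be 7 × √(1,912 / 10.507) = 94.4 mmHg, which is 94.4 / √1.4 = 79.8 mmHg per visit at correlation 0.3.

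**Power with 1,912 evaluable, paired, stated inputs.**
- SE = 59.16 / √1,912 = 1.353 mmHg.
- Power for 7 mmHg = Φ(7 / 1.353 − 1.96) = Φ(3.21) = 0.9993.
- Change detectable with 90% power = 3.2416 × 1.353 = 4.39 mmHg.
- 95% CI half-width = 1.96 × 1.353 = 2.65 mmHg.

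**After losses.** 1,912 × 1.2 = 2,294.4, which matches the stated 2,294. A 20% loss from 2,294 leaves 0.8 × 2,294 = 1,835, not 1,912; keeping 1,912 would take 1,912 / 0.8 = 2,390. With 1,835 evaluable, SE = 59.16 / √1,835 = 1.381, the 90%-power change is 4.48 mmHg, the half-width is 2.71 mmHg, and power for 7 mmHg is still 99.9%.

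**Nearest formula that keeps every stated input.** Two-arm comparison adjusted for baseline (ANCOVA): 2 × 10.507 × 2,500 × (1 − 0.3²) / 49 = 975.7, so 976 per arm and 1,952 in total. That is 2.1% above 1,912, close but not equal.

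**The case against.** The strongest case on the other side is that the mismatch shows less than it seems to.

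- **The error is conservative.** Under the stated inputs the primary analysis has about 99.9% power, so the study is not put at risk, and the planned 95% confidence intervals will show the size of any change. This stands. It makes the 90% an understatement, but it does not make the calculation right.
- **A design effect may be hidden in the number.** Participants are grouped by nursing assistant, district or municipality, and primary care center, and recruitment is spread across provinces. An inflation of about 2.5 would account for 1,912, and a fuller protocol might state it. This cannot be excluded. But the article presents 1,912 as the result of the listed inputs and adds only the loss allowance afterwards, so such a factor would still need to be stated.
- **A reader might infer that a two-arm formula was used.** The document does not support that as fact. With every stated input kept, two-arm ANCOVA gives 1,952. Matching 1,912 takes a changed input: 5 mmHg instead of 7 (1,912.35 per arm), or correlation 0.33 instead of 0.3 (956 per arm).
- **A reader might also infer that the assumptions are wrong, above all the SD of 50.** It does look large for blood pressure. But the article gives no expected baseline mean or spread to test it against, and one of its three entry criteria sets no blood pressure threshold. This is a query for the sponsor, not a demonstrated error.

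**Conclusion.** The point holds on its arithmetic. The 1,912 is about 2.5 times the 751 to 753 that the stated inputs need in the stated design, and about 3.5 times the 539 needed if SD 50 is the SD of the change (1,912 / 539 = 3.55). At least one of the number, the inputs and the design description must be wrong or incomplete, and the document does not show which. It does not establish that the 7 mmHg, the SD or the correlation is wrong, nor that a between-group formula was applied.

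The study is not underpowered for 7 mmHg on its own assumptions. These results assume one paired comparison of baseline with 12 months, independent participants and no design effect. If clustering is material, the power and precision shown here would be lower.

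**What to change.** Keep the recruitment target and rewrite the Sample size paragraph for the paired single-arm design:

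1. Name the formula, and withdraw any between-group formula if one was used.
2. Say whether SD 50 is a per-visit SD or the SD of the change, and justify its size.
3. If an allowance for clustering is included, state the design effect and its basis.
4. Replace the 90% power claim with what the target delivers. With the current inputs read as a per-visit SD, and no design effect, that is 90% power for about 4.4 mmHg and a 95% CI half-width of about 2.7 mmHg with 1,912 evaluable, or about 4.5 mmHg and 2.7 mmHg with the roughly 1,835 left after a 20% loss from 2,294.

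The cost is one reworded paragraph. Recruitment, the primary outcome and the analysis do not change.

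### Enrolling 2,294 covers a loss of about 16.7%, not the stated 20%: a minor error in the loss tolerance, which does not show that the trial is underpowered

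*Protocol article*

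**What the plan says.** All the figures are in the Sample size section of the protocol article. The calculation "assumed a 7-mmHg reduction in SBP (SD 50) after 12 months of follow-up", with "a correlation of 0.3 between baseline and follow-up measurements", 90% power and a two-sided 5% level. From these, "the required initial sample size was estimated at 1,912 participants", "increasing to a final sample size of 2,294 after allowing for approximately 20% lost". The formula for the loss allowance is not given.

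Two other sections bear on the point. Study design describes a single-arm study that compares each participant's follow-up with his or her own baseline. Clinical effectiveness outcomes, in the analysis plan, says that missing outcomes are not imputed and that the mixed model is fitted to the data observed. The primary outcome is the change in systolic pressure from baseline to 12 months.

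**The concern.** A loss rate is a share of the people enrolled. To end with a required number, one divides that number by the share expected to remain. The printed figure instead matches the required number with 20% of itself added, which always allows for less than the nominal loss.

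What is at stake is the retention tolerance that the article publishes. With loss anywhere between 16.7% and 20%, the study would be within its stated allowance and yet below its stated requirement. At 18% loss, for example, 2,294 × 0.82 = 1,881 remain.

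**Working it through.** **Inputs (Sample size section).** Reduction 7 mmHg; SD 50, without saying whether of a single measurement or of the change; correlation 0.3; power 90%; two-sided 5%; required number 1,912; loss 20%; final number 2,294. z(0.975) + z(0.90) = 1.960 + 1.282 = 3.2415.

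**1. Reproducing the final figure.**
- Multiplying: 1,912 × 1.2 = 2,294.4, which rounds to the printed 2,294.
- Dividing: 1,912/(1 − 0.20) = 2,390, which is 96 more than 2,294 and does not match.

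**2. What 2,294 delivers.**
- At 20% loss: 2,294 × 0.80 = 1,835 with a 12-month value.
- Shortfall: 1,912 − 1,835 = 77, and 77/1,912 = 4.0%.
- Loss that still leaves 1,912: 1 − 1,912/2,294 = 16.7%.

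**3. Power, taking 1,912 at face value.** If 1,912 gives exactly 90%, power at 1,835 is Φ(3.2415 × √(1,835/1,912) − 1.960) = Φ(1.216) = 88.8%.

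**4. Power from the stated inputs under the design described.**
- If 50 is the SD of a single measurement, the SD of the change is 50 × √(2 × (1 − 0.3)) = 59.16. Then n = (59.16 × 3.2415/7)² = 750.5, so 751.
- If 50 is already the SD of the change, n = (50 × 3.2415/7)² = 536.1, so 537.
- Power at 1,835 with SD 59.16: Φ(7 × √1,835/59.16 − 1.960) = Φ(3.11), over 99.9%. With SD 50 it is higher still.
- Half-width of the 95% confidence interval with SD 59.16: 1.960 × 59.16/√1,912 = 2.65 mmHg and 1.960 × 59.16/√1,835 = 2.71 mmHg.

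**5. The base figure.** Neither paired reading gives 1,912. Of the one- and two-sided variants tried at 90% power, only a two-arm total with baseline adjustment comes within 3%: 2 × (50 × 3.2415/7)² × (1 − 0.3²) = 975.7, so 976 per arm and 1,952 in total. On that reading power is 89.4% at 1,912 and 88.2% at 1,835. The article does not say that this formula was used, and the study has one arm.

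**The case against.** The strongest objection is that nothing of consequence follows. A reader might infer from the shortfall that the trial is underpowered. The document does not support that: the loss of about one power point depends on 1,912 being exactly the number for 90%, and the stated inputs do not yield 1,912 for a single-arm paired comparison. Even 751 divided by 0.8 is only 939, far below 2,294. This objection stands, and it limits the point to the stated tolerance.

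Second, the base figure is the larger problem, and if it is revised then 2,294, 2,390 and the shortfall of 77 all change. That is true. But the inflation step would still under-allow for 20% loss if the same multiplication were applied to a new base.

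Third, the mixed model uses the earlier visits of participants lost before month 12. So 1,835 counts those with a 12-month value, not those contributing to the model, and the information lost is probably less than the head count suggests. This stands as a caution on wording. It does not reconcile the figures, because the allowance is stated as a head count and takes no credit for partial follow-up.

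Fourth, the article says "after allowing for approximately 20% lost" and gives no formula, so the multiplication is inferred from the match. The inference is strong, since 20% added to 1,912 gives the printed number after rounding. Calling the rate approximate does not help: the calculation appears to have used 20% itself, applied to the wrong base.

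**Conclusion.** The point holds as a minor arithmetic error. On the article's own figures, 2,294 protects 1,912 against a loss of 16.7%, not 20%; at 20% loss it leaves 1,835, which is 77 (4.0%) too few. This part needs no assumption beyond reading the loss rate as a share of those enrolled.

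The effect on power is conditional. It is about 88.8% instead of 90% if 1,912 is accepted as exact. It stays over 99.9% if the paired calculation with the stated inputs applies, with either meaning of the SD. The finding therefore corrects a published tolerance and gives no ground for calling the sample too small.

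**What to change.** Keep 2,294 and change the sentence: state that it allows for about 17% loss (16.7% exactly) relative to 1,912, and that at 20% loss 1,835 would have a 12-month value. Beside it, give the power or the confidence interval width at 1,835 from a calculation that matches the within-participant design, saying which SD the 50 is. If the base figure is revised, obtain the enrolment target by dividing it by one minus the expected loss.

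The cost is one or two sentences and a slightly less favourable stated tolerance. No extra enrolment and no change to the analysis is needed.

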### Analysis plan

#### Qualitative analysis

A deductive analysis will be conducted using Nvivo software, version 1.6.1., through open coding of focus group narratives. Iterative reading will enable the identification and refinement of core categories (facilitators and barriers) and emerging subcategories until thematic saturation is achieved. During the interview process, credibility will be ensured using follow-up questions predefined in the interview guide. Subsequently, the findings will be discussed with two participants to ensure confirmability.

#### Clinical effectiveness outcomes

Descriptive analyses will summarize continuous variables using means or medians, along with standard deviations or interquartile ranges, depending on the distribution of the data. Absolute and relative frequencies represent categorical variables. For the primary and secondary outcomes, the analysis will produce estimates using linear mixed models of the continuous outcomes (change in systolic blood pressure, systolic and diastolic blood pressure), and generalized linear mixed models for the categorical outcomes (proportion of hypertension control, proportion of modification of life styles, proportion of participants in low, moderate, high and extremely high cardiovascular risk), estimating mean and 95% confidence intervals at baseline and 3, 6, 9, and 12 months of follow-up. The models will include random intercepts accounting for within-subject correlation over time, and the fixed effects will include sex, region, age and anthropometric measures. We will impute missing covariate data using the predictive mean matching algorithm implemented in the mice package (version 3.16) in R statistical software (version 4.3). We will not impute missing outcome because these are expected to be approximately missing at random, primarily due to participants moving out of their municipality of residence. Accordingly, the mixed-effects model will be fitted using the observed data. Finally, we will perform a sensitivity analysis comparing the primary and secondary outcomes between participants who are aware of their condition and receiving treatment and those who are unaware of their condition. The mixed-effects models will be fitted using the lme4 (version 1.1-35.1) and mgcv (version 1.9-1) packages in R.

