### Population and sample

Adults aged ≥18 years be selected through convenience sampling from the community based on the following criteria: a) newly diagnosed hypertension (defined as blood pressure ≥140/90 mmHg); b) uncontrolled hypertension (defined as blood pressure ≥140 mmHg in individuals with a previous diagnosis of hypertension or who are currently on antihypertensive treatment); and/or c) known hypertensive individuals not regularly attending cardiovascular risk management programs at primary care centers. Exclusion criteria include established cardiovascular disease (e.g., coronary artery disease, myocardial infarction, heart failure, arrhythmias, cardiomyopathies, peripheral arterial disease, stroke or transient ischemic attack, diabetes mellitus with macrovascular complications, or history of invasive cardiovascular procedures), chronic kidney disease requiring dialysis, intolerance to antihypertensive medications, and resistant or secondary hypertension. The exclusion of these people was based on the fact that these pathologies require individualized and specialized management at high levels of care, which exceeds the capabilities of a community-based strategy.

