### Secondary outcomes

After 12 months, the intervention will be assessed for its impact on blood pressure control (systolic blood pressure <140 mmHg) with a target of control around 60% of participants and the adoption of healthy behaviors, including increased physical activity and reduced tobacco and alcohol use compared to baseline. Improvements in participants' understanding of hypertension, its treatment, and the importance of regular medical follow-up may be observed. Additionally, the strategy will be evaluated for its potential to reduce the incidence of fatal and non-fatal myocardial infarction and stroke. The implementation of CHWs may contribute to improve participants' perceptions of support, trust, and accessibility to primary healthcare.

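### Visit proportions taken from random-intercept GLMMs at a random effect of zero would not estimate the population proportions that the outcomes define; the plan should commit to population-averaged figures

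*Protocol article*

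**What the plan says.** In the protocol article, Outcomes and measurements lists among the secondary outcomes "Proportion of participants achieving systolic blood pressure control (<140 mmHg) from baseline to 12 months" and "Changes in the prevalence of healthy behaviors". Both are statements about a population of participants. Under Expected results, Secondary outcomes, the article adds a benchmark on the same scale: "with a target of control around 60% of participants".

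Clinical effectiveness outcomes, in the analysis plan, assigns linear mixed models to the continuous outcomes and "generalized linear mixed models for the categorical outcomes (proportion of hypertension control, proportion of modification of life styles" and the cardiovascular risk categories). On structure it says: "The models will include random intercepts accounting for within-subject correlation over time". The stated output is "estimating mean and 95% confidence intervals at baseline and 3, 6, 9, and 12 months of follow-up". On software: "The mixed-effects models will be fitted using the lme4 (version 1.1-35.1) and mgcv (version 1.9-1) packages in R".

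The section names no link function. It also does not say whether the visit means of the GLMMs are predicted at a random effect of zero or averaged over the random effects. Separately, it plans simple counts and percentages as descriptive summaries of categorical variables.

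**The concern.** A linear mixed model has an identity link, so its fixed-effect visit mean is also the population mean. The systolic pressure analysis therefore has no such gap. With a non-linear link the two separate. The back-transformed fixed effect of a random-intercept logistic model is the probability for a participant whose random effect is zero, and that differs from the proportion of participants with the outcome. The section describes both model classes in one sentence with one output, as though their means could be read in the same way.

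The study has a single arm and judges control by its change from baseline and by a level of about 60%. The scale of the estimate therefore feeds directly into the conclusion. An interval built at a random effect of zero is centred on a different quantity, and a larger sample only tightens it around that quantity.

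**Working it through.** The article derives no figure on this point, so there is nothing to reproduce. The check asks what the random-effect-zero prediction would show for a given true proportion.

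**Inputs**
- Control at 12 months: 60%, the target under Expected results.
- Control at baseline: not given. It need not be zero, because one entry route, "known hypertensive individuals not regularly attending cardiovascular risk management programs at primary care centers", carries no blood pressure threshold. Assumed 15%, with 5% to 40% as the range.
- Link: logit, assumed.
- Random-intercept variance s²: not given. It is set through an assumed latent correlation ρ by s² = ρ/(1 − ρ) × π²/3. This gives s² = 1.41 at ρ = 0.3, 3.29 at 0.5 and 4.93 at 0.6. The 0.3 in the Sample size section is a correlation for systolic pressure, so it is only a guide here.

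**Formula.** For a true proportion p, solve E[expit(η + sZ)] = p for η, with Z standard normal. The random-effect-zero prediction is expit(η).

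**Control, true 15% to 60% (rise 45 points)**

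| ρ | baseline reads as | month 12 reads as | rise reads as |
|---|---|---|---|
| 0.3 | 10.3% | 62.7% | 52 points |
| 0.5 | 6.9% | 65.3% | 58 points |
| 0.6 | 5.1% | 67.1% | 62 points |

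Hand check at ρ = 0.3 with the usual approximation η ≈ logit(p) × √(1 + 0.346 s²), where 0.346 = (16√3/15π)². The factor is √(1 + 0.346 × 1.41) = 1.22. For 60%, 0.405 × 1.22 = 0.495, or 62.1%. For 15%, −1.735 × 1.22 = −2.116, or 10.8%. Both are close to the exact values.

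With month-12 control held at 60%, baseline at 5% to 40% and s² from 0.5 to 6, the rise was overstated in every case. The smallest excess was 2 points (5% to 60% at s² = 0.5 reads as 57.0 against 55). The largest was 21 (30% to 60% at s² = 6 reads as 51.0 against 30).

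**The direction is not fixed.** Change in points, read at a random effect of zero:

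| true change | s² = 1 | s² = 3.29 | s² = 6 |
|---|---|---|---|
| 5% to 30% (25) | 23.2 | 19.8 | 16.5 |
| 10% to 30% (20) | 19.4 | 17.5 | 15.1 |
| 10% to 40% (30) | 30.8 | 30.9 | 29.8 |

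For lifestyle behaviours (illustrative values), a prevalence falling from 12% to 8% reads as 8.8% to 5.6% at s² = 1 and 2.8% to 1.4% at s² = 6. The 4-point fall shrinks to 3.2 or 1.4. A prevalence rising from 30% to 45% reads as 26.5% to 44.0%, or 17.1% to 40.7%, so that change is overstated.

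**Intervals.** Simulations used 1,835 participants (2,294 × 0.8), five visits, a visit-only logistic model and true control of 15% to 60%. The 95% interval at a random effect of zero missed the true 60% in 49% of runs at ρ = 0.3 and 82% at ρ = 0.5. When control was generated instead by thresholding normally distributed pressures, the misses were 35% and 78%. Integrating the same logistic fits over the random intercept returned 15.0% and 60.0%.

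**The case against.** The strongest reply is that the plan never says predictions will be taken at a random effect of zero. The same fitted model gives the right proportion once it is averaged, and a condensed article may leave post-estimation steps to the full analysis plan. Much of this stands. A reader might infer that the reported proportions will be wrong; the text does not support that, because it fixes the model and the output but not the step between them. The point survives because the article does fix the model, the random effect, the visit-level output and the software, against outcomes defined as population proportions. The usual fixed-effect reading of that combination misses the stated quantity.

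A reader might also infer that the rise in control must be overstated. That holds near the 60% target, but the second table shows it can reverse. Nor does the plan test anything against 60%: the figure is an aspiration, so the missed-interval rates above measure coverage and do not describe a planned decision.

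The sizes rest on assumed variances and an assumed baseline. At ρ = 0.3 the month-12 level moves by less than 3 points, against a target worded loosely. The planned covariates (sex, region, age, anthropometry) would absorb some between-person variance and so shrink the gap.

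Finally, crude percentages are planned, and a large discrepancy beside them would be noticed. They do not correct the model's intervals, however. They also do not replace the model where the plan relies on missing outcomes being missing at random.

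**Conclusion.** The concern holds in conditional form. If the GLMM visit means are read at a random effect of zero under a logit link, they do not estimate the proportions that the article defines, and the changes from baseline are biased as well. At the article's own target the rise in control would look larger than it is, by about 7 points (15% to 60%, ρ = 0.3) or 13 points (ρ = 0.5) in the worked example. With lower final control, or for uncommon behaviours, it could look smaller. These sizes assume the link, the random-intercept variance and the baseline level. The movement away from 50% applies to yes/no outcomes; for the four risk categories the mismatch applies, but the direction depends on how they are modelled. Only secondary outcomes are affected.

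**What to change.** Keep the GLMM. Add to Clinical effectiveness outcomes that visit proportions and their changes from baseline are population-averaged: fitted probabilities are integrated over the estimated random-intercept distribution and averaged over the observed covariates. Take 95% intervals from a bootstrap over participants or from the delta method. Report these beside the observed proportion at each visit, and use them when reading the result against the 60% target. Apply the same rule to control, to each lifestyle behaviour as a prevalence at each visit, and to the cardiovascular risk categories. Name the link function in the same sentence.

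The cost is one or two sentences and a few lines of R, with no new data or participants. The reported improvement in control may be smaller than the random-effect-zero figure would have shown.
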